### Definition of serious adverse event (SAE)

An adverse event will be considered a Serious Adverse Event (SAE) if it meets any of the following criteria:

1. Results in death.
2. Is life-threatening (defined as an event that poses an immediate threat to the patient's life at the time of occurrence, rather than a hypothetical situation where the event would lead to death if it were more severe).
3. Results in persistent or significant disability/incapacity.
4. Requires inpatient hospitalization or prolongation of existing hospitalization.
5. Involves congenital anomaly/birth defect.
6. Other important medical events.

### Severity of AEs

The severity of Adverse Events (AEs) is evaluated according to the general grading principles of the National Cancer Institute's Common Terminology Criteria for Adverse Events (CTCAE v5.0), which are divided into five levels:

**Grade 1**: Mild; asymptomatic or only mildly symptomatic; detected only clinically or by diagnostic studies; intervention not indicated.

**Grade 2**: Moderate; minimal, focal, or non-invasive intervention indicated; limited age-related instrumental activities of daily living.

**Grade 3**: Severe or medically significant but not immediately life-threatening; inpatient hospitalization or prolongation of existing hospitalization indicated; disability; self-care activities of daily living limited.

**Grade 4:** Life-threatening; urgent intervention indicated.

**Grade 5**: Death related to the AE.

### Management of AEs

When an AE occurs, the investigator will take appropriate management measures based on the severity of the event. If the symptoms are mild and consistent with the common toxic side effects previously observed with perospirone, dose reduction, temporary discontinuation of the drug, and close monitoring may be implemented, with timely adjustments as needed. If the symptoms are severe or beyond the scope of common toxic side effects, the drug should be discontinued immediately. Additional necessary laboratory tests and assessments should be conducted to determine the severity of the AE and its corresponding impact. Symptomatic treatment will be provided based on clinical manifestations and test results. The costs associated with these additional tests and assessments will be covered by the sponsor. Regardless of the severity of the adverse event, the investigator must document the entire process in detail.

If the occurrence of an AE compromises the rights and safety of the participant, the sponsor will assume relevant responsibilities in accordance with national laws and regulations, covering the costs of related treatments and providing appropriate financial compensation. In the event of rare or new SAEs that fall outside the expected scope, the sponsor will organize consultations with the patient and their family members to provide reasonable financial compensation.

### Causality assessments

Physicians who examine and assess participants must evaluate the causality of all AEs in relation to the study intervention based on temporal relationships and their clinical judgment. The certainty of causality will be graded using the following categories:

**Definitely related to the study drug:** There is evidence of taking the investigational medication; the temporal sequence between the occurrence of the AE and the intake of the study drug is credible; the AE is more reasonably explained by the study drug than by other causes; positive dechallenge reaction; positive rechallenge reaction; the pattern of the AE is consistent with prior knowledge of this or similar drugs.

**Probably related to the study drug:** There is evidence of taking the study drug; the temporal sequence between the occurrence of the AE and the intake of the study drug is credible; the AE is more reasonably explained by the study drug than by other causes; positive dechallenge reaction.

**Possibly related to the study drug:** There is evidence of taking the study drug; the temporal sequence between the occurrence of the AE and the intake of the study drug is credible; the AE may be caused by the study drug but could also be due to other causes; positive dechallenge reaction.

**Possibly unrelated to the study drug:** There is evidence of taking the study drug; the AE is more likely due to other causes; negative or equivocal dechallenge reaction; negative or equivocal rechallenge test.

**Definitely unrelated to the study drug:** The participant did not take the study drug; or the temporal sequence between the occurrence of the AE and the intake of the study drug is not credible; or there are other significant causes that could explain the AE.

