**Note:**

- Medical History includes current illness, past medical history, personal history, marital and reproductive history, menstrual history, and family history.
- Safety Assessments include vital signs, physical examination, complete blood count, blood glucose, blood lipids, liver and kidney function tests, urinalysis, and ECG.
- Specific examination items are detailed in the study schedule.
- Adverse events must be promptly recorded and assessed for their relationship with the treatment using perospirone tablets. Those assessed as definitely related, possibly related, or probably related are considered drug-related adverse reactions.

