## Adverse event (AE) and serious adverse event (SAE)

### Definition of adverse event (AE)

An Adverse event (AE) is defined as any untoward medical occurrence in a participant associated with the use of the study medication or occurring during the study, regardless of whether there is a causal relationship with the study medication or treatment process.

Endpoint events are not considered AEs unless, based on the investigator's best clinical judgment, considering the course, severity, or other characteristics of the event, it should be regarded as an exception in this clinical context.

Any AE, regardless of its severity or whether it is related to the study medication, should be recorded in the CRF from the time the participant signs the informed consent form until the end of the last scheduled visit as planned in the study protocol. The investigator should specifically describe the timing of the event, its severity, any actions taken regarding the study medication, symptomatic treatment provided, outcomes, and his/her judgment on whether the AE might have been caused by the study medication.

Laboratory test results, vital signs, or ECG abnormalities will be recorded as AEs if they are medically related to the study medication, such as when accompanied by clinical symptoms, necessitating symptomatic treatment, leading to discontinuation of the medication, or resulting in serious consequences.

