### Requirements for AE recording and follow-up

When participants receiving medical services during visits or monitors conducting reviews, the occurrence of AEs or SAEs should draw the attention of researchers.

All AEs that do not meet the criteria for SAEs will be recorded in the CRF, including both local and systemic reactions. Information to be collected includes a description of the event, onset time, assessment of severity by a physician, relationship to the investigational medication (which can only be assessed by trained personnel with diagnostic authority), and the time when the event is resolved or stabilized. All AEs occurring during the study must be comprehensively documented, regardless of their relationship to the study intervention. All AEs should be followed up until reasonably resolved.

Medical conditions at the time of participant screening should be considered baseline and not reported as AEs. However, if the participant's condition worsens at any time, it should be recorded as an AE.

Changes in the severity of AEs should be documented to assess the duration of the event at different severity levels. Intermittent AEs require recording of onset time and the duration of each onset.

From the time of signing the informed consent form to the end of the trial, investigators should record all AEs/SAEs. At each visit, researchers should inquire about AEs/SAEs that occurred since the last visit and follow up on the outcome of the events until they are resolved or stabilized.

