For the primary efficacy outcomes and partial secondary efficacy outcomes (i.e. response and remission rates at weeks 4 and weeks 8), last observation carried forward (LOCF) method was used to handle the missing data in the anaysis of these outcomes. Since these outcomes were defined based on MADRS scores at the corresponding visit (response: ≥50% reduction from baseline; remission: MADRS score ≤10), missing MADRS values in the FAS were imputed using LOCF, and response or remission status was subsequently determined based on the imputed scores. Logistic regression models were employed to analyze and compare these outcomes between the the perospirone + SSRIs/SNRIs group (perospirone group) and the placebo + SSRIs/SNRIs group (placebo group), using results of the placebo group as reference. In the logistic regression model, treatment group was included as factor, and baseline MADRS total score was included as a covariate.

For the other secondary efficacy measures, the mean change of the included scales (MADRS, QIDS-SR16, HAMA, and Q-LES-Q-SF) from the baseline (Week 0) to Week 4 and Week 8 were analyzed. The mean changes and the differences of the mean changes of the secondary efficacy outcomes between the perospirone group and the placebo group were calculated and compared through the use of a mixed model for repeated measures (MMRM) analysis (with an unstructured covariance matrix). This method is widely recommended for longitudinal data with missing values under the missing at random (MAR) assumption, as it utilizes all available data and does not require explicit imputation. The model included the baseline total scores of each scales, study centre (centre 1 to centre 10), treatment group (perospirone and placebo), time (week 2, week 4 and week 8), and time-by-treatment interaction as fixed effects, with the subjects-specific effects as a random effect. The least squares mean (LSM) changes of the scores for the two groups were reported.

Chi-square tests or Fisher’s precision probability tests were conducted to compare the overall incidence rates of AEs, SAEs and AEs leading to treatment discontinuation, as welll as the incidence rates of each drug related-AE between the two groups. All statistical analyses were done in Statistical Analysis System (SAS) version 9.4. Statistical significance was determined by a two-sided p value less than 0.05

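### The event-by-event AE comparison is limited to drug-related AEs, and every related grade lists a positive dechallenge, so AEs tolerated on unchanged drug can be left out and individual harms understated

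*Protocol*

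**What the plan says.** **Causality grades (Protocol 8.4.5).** Definitely, probably and possibly related each list a positive dechallenge. For possibly related the text is "the AE may be caused by the study drug but could also be due to other causes; positive dechallenge reaction". The next grade down, possibly unrelated, reads "the AE is more likely due to other causes; negative or equivocal dechallenge reaction; negative or equivocal rechallenge test". No grade provides for a dechallenge that was not done. The section opens by saying that physicians "must evaluate the causality of all AEs in relation to the study intervention based on temporal relationships and their clinical judgment".

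**What counts as drug-related (note to the flowchart, 1.2).** "Those assessed as definitely related, possibly related, or probably related are considered drug-related adverse reactions".

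**Analysis (section 12, item 5).** Overall AEs, SAEs and AEs leading to discontinuation are compared between arms without reference to cause. Event by event, the comparison covers "the incidence rates of each drug related-AE between the two groups".

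**Recording.** Section 8.4.1 states the general rule: "Any AE, regardless of its severity or whether it is related to the study medication, should be recorded in the CRF". Section 8.4.6 repeats it: "All AEs occurring during the study must be comprehensively documented, regardless of their relationship to the study intervention". The last paragraph of 8.4.1 departs from it for laboratory results, vital signs and ECG abnormalities, which "will be recorded as AEs if they are medically related to the study medication". Section 7.1, on laboratory changes after enrolment, says that any new clinically relevant finding is reported as an AE, with no condition on cause.

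**The concern.** In a randomised double-blind trial, the comparison between arms is itself the evidence on causation. Selecting events first by individual judgement can remove true cases and does not improve that comparison.

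Here the selection depends on whether the drug was interrupted. Section 8.4.4 makes dose reduction or temporary discontinuation optional for mild, expected events, so an event can run its course with no dechallenge. The events most exposed are those that patients tolerate while continuing. Section 2.2.1 names akathisia (25.4%), insomnia (21.7%) and tremor (15.2%) among the drug's common effects; a tolerated case of any of these could miss a related grade.

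The laboratory, vital-sign and ECG rule raises a second, separate problem. Section 3 names liver and kidney function and ECG abnormalities as parts of the AE-incidence endpoint. If sites follow different recording rules, that part of the endpoint is not counted uniformly.

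**Working it through.** **Step 1. Follow an event in a patient who continues unchanged.**

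| Rule | Effect on an event with no dechallenge |
|---|---|
| 8.4.5 definitely, probably, possibly related | Each lists a positive dechallenge, so none is met in full |
| 8.4.5 possibly unrelated | Lists a negative or equivocal dechallenge, so not met in full |
| 8.4.5 definitely unrelated | Needs no drug intake, an implausible time sequence or another significant cause, so not met by a plausible drug effect |
| 1.2 note | Only the three related grades count as drug-related |
| Section 12, item 5 | Only drug-related AEs enter the per-event comparison |

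The event falls between the grades. Read literally, it cannot be drug-related and so cannot enter the per-event comparison. If investigators fall back on the clinical judgement allowed in the opening sentence of 8.4.5, some will grade it possibly related and others will not. The protocol does not say whether a dose reduction counts as dechallenge.

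**Step 2. Effect on the risk difference.** Let p1 and p0 be the true event proportions on drug and placebo, and f the share of events that obtain a related grade, assumed equal in both arms. The comparison then sees f·p1 and f·p0, and the difference is f·(p1 − p0).

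**Step 3. Effect on power (illustration).** The protocol states no figure for this, so there is none to reproduce. Inputs:

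- n1 = 108 and n0 = 102, the numbers included per arm (Synopsis).
- p1 = 0.254, akathisia in the pre-approval studies in Japan (2.2.1; 109/429 = 0.254), borrowed as an assumption.
- p0 = 0.05 or 0.10, assumed.
- Two-sided alpha 0.05 (section 12, item 5).
- f is not given, so 1 to 0.25 is shown.

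Formula: power = Φ[(d − 1.96·se0)/se1], where d = f(p1 − p0), se0 = √[p̄(1 − p̄)(1/n1 + 1/n0)], p̄ is the pooled proportion, and se1 = √[fp1(1 − fp1)/n1 + fp0(1 − fp0)/n0].

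Example with p0 = 0.05 and f = 0.5: the proportions are 0.127 and 0.025, so d = 0.102, p̄ = 0.0775, se0 = 0.0369 and se1 = 0.0356. Then (0.102 − 1.96 × 0.0369)/0.0356 ≈ 0.83, giving power of about 0.80.

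| f | Difference, p0 = 5% | Power | Difference, p0 = 10% | Power |
|---|---|---|---|---|
| 1 | 20.4 points | 98.8% | 15.4 points | 83.6% |
| 0.75 | 15.3 | 94.2% | 11.6 | 69.3% |
| 0.5 | 10.2 | 79.8% | 7.7 | 49.7% |
| 0.25 | 5.1 | 48.1% | 3.9 | 26.7% |

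**Step 4. Sensitivity of a single test result (Fisher exact).** Unfiltered, 27/108 against 5/102 gives p = 0.00004. With about 30% retained, 8/108 against 2/102 gives p = 0.10, but 8/108 against 1/102 gives p = 0.036 (30% of 5 is 1.5, so either rounding is possible). With about half retained, 13/108 against 2/102 or 3/102 gives p = 0.006 or 0.017.

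**Step 5. The recording rules side by side.** The general rule in 8.4.1 and the rule in 8.4.6 set no condition on cause, nor does 7.1 for clinically relevant findings. The last paragraph of 8.4.1 does, for laboratory, vital-sign and ECG abnormalities. A clinically relevant laboratory change judged unrelated is an AE under 7.1 and not an AE under that paragraph.

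**The case against.** The strongest case on the other side is that most of the safety analysis is unfiltered.

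- **Recording.** A reader might infer that AEs are filtered by cause when they are recorded. The general rule in 8.4.1 and section 8.4.6 say the opposite. Only laboratory, vital-sign and ECG abnormalities carry a condition, and the examples given there (symptoms, need for treatment, discontinuation, serious consequences) read like a clumsily worded test of clinical significance. This stands.
- **Laboratory data.** Section 8.2 compares the proportions of abnormal laboratory and vital-sign results by arm, and 9.2.4 tabulates normal and abnormal laboratory changes. Those data are not lost, whatever is recorded as an AE. This stands.
- **Other analyses.** A reader might infer that tolerated harms vanish from every comparison. Section 12, item 5 itself compares overall AEs, SAEs and AEs leading to discontinuation without a filter. Sections 9.2.3 and 9.2.4 count any TESS score above zero as an event and test TESS items by arm, and 9.2.4 tabulates all AEs. This stands, with limits: section 12 neither mentions nor withdraws the TESS comparison; that comparison needs at least one follow-up visit; and a table is not a between-arm comparison.
- **Grading.** A reader might infer that an event with no dechallenge must be called unrelated. The text does not assign it there; it leaves a gap, and clinical judgement may fill it. This stands, but it replaces exclusion with inconsistent grading across 10 centres.
- **Size.** A reader might infer that a clear signal would disappear. Step 4 shows that this depends on an assumed 30% retention and on how 1.5 cases are rounded. The documents do not support it.

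**Conclusion.** The point holds in a limited form. The one between-arm comparison of individual AEs named in section 12, item 5 is restricted to drug-related events, and the grading scale gives no route to a related grade for an event in which the drug was not interrupted. Individual harms can therefore be understated.

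The risk difference shrinks in proportion to f. In the illustration, power falls from about 99% to 80% at f = 0.5 and 48% at f = 0.25 with a 5% placebo rate, and from about 84% to 50% and 27% with a 10% placebo rate. This rests on an akathisia rate from other studies, assumed placebo rates, and an f that is equal in both arms and unknown. If f differed between arms, the distortion would be f1·p1 − f0·p0 against p1 − p0, and its size could not be stated in advance.

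The conflict between the last paragraph of 8.4.1 and sections 7.1 and 8.4.6 is real but separate. It is softened by the by-arm comparison of abnormal results in 8.2.

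**What to change.** 1. **Section 12, item 5:** compare each treatment-emergent AE by arm regardless of causality, and give drug-related AEs as a supplementary table. State whether the TESS item comparison in 9.2.4 is kept.
2. **Section 8.4.5:** remove positive dechallenge as a condition of possibly related, and add an entry for dechallenge not done.
3. **Section 8.4.1:** reconcile the recording rule for laboratory, vital-sign and ECG abnormalities with the general rule in the same section and with 7.1 and 8.4.6.

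The first change uses data that 8.4.6 already requires on the CRF, and for data already collected it corrects the main problem without regrading any event. The other two are changes of wording. The cost is a longer AE table.

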### Requirements for AE recording and follow-up

When participants receiving medical services during visits or monitors conducting reviews, the occurrence of AEs or SAEs should draw the attention of researchers.

All AEs that do not meet the criteria for SAEs will be recorded in the CRF, including both local and systemic reactions. Information to be collected includes a description of the event, onset time, assessment of severity by a physician, relationship to the investigational medication (which can only be assessed by trained personnel with diagnostic authority), and the time when the event is resolved or stabilized. All AEs occurring during the study must be comprehensively documented, regardless of their relationship to the study intervention. All AEs should be followed up until reasonably resolved.

Medical conditions at the time of participant screening should be considered baseline and not reported as AEs. However, if the participant's condition worsens at any time, it should be recorded as an AE.

Changes in the severity of AEs should be documented to assess the duration of the event at different severity levels. Intermittent AEs require recording of onset time and the duration of each onset.

From the time of signing the informed consent form to the end of the trial, investigators should record all AEs/SAEs. At each visit, researchers should inquire about AEs/SAEs that occurred since the last visit and follow up on the outcome of the events until they are resolved or stabilized.

### AE reporting

Investigators should inform participants to truthfully report any changes in their condition following medication use. Physicians should avoid leading questions. While observing treatment efficacy, attention should also be paid to AEs or unexpected toxic side effects (including symptoms, signs, and laboratory test results). Investigators should analyze the causes, make judgments, and calculate the incidence of AEs.

For AEs occurring during the study, symptoms, severity, onset time, duration, management measures, and course of the event should be documented in the CRF. The relationship between the AEs and the investigational medication should be evaluated, and the form should be signed by the investigator with the date noted.

### SAE reporting

In the event of a SAE occurring during the study, the investigator shall immediately (usually within 24 hours of becoming aware) provide the sponsor with a written report of all SAEs, followed by a timely, detailed, and written follow-up report. SAE reports and follow-up reports should include the participant's identification code used in the clinical trial, rather than the participant's real name, national identity number, address, or other personal identification information.

Upon receiving any safety-related information from any source, the sponsor shall immediately conduct a comprehensive analysis, assessment, and judgment of the SAE. If it meets the definition of a Suspected Unexpected Serious Adverse Reaction (SUSAR), the sponsor is required to send the processed SUSAR report and follow-up report to the investigator within the specified timeframe.

For reports involving fatal events, the investigator shall provide the sponsor and the ethics committee with any additional required information, such as autopsy reports and final medical reports.

### Reporting AEs/SAEs to participants

After the occurrence of an AE/SAE, active management is required. Following the investigator's assessment of causality, timely communication with the patient is necessary to seek the patient’s opinion on whether to continue participating in the study and receiving the intervention.

